### Objectives

The long-term objectives of this study are the investigation of the predictive validity of early cognitive profiles in PD and identification of genetic and magnetic resonance imaging (MRI) markers signaling more rapid conversion to dementia. In this study, we will target the posterior cortex as a reliable marker of pathologic burden based on the proposed caudal-rostral progression of α-synuclein and the rostrocaudal dopamine gradient, with lower occipital receptor density eliminating the effects of dopamine replacement therapy (DRT). Our hypothesis, based on the models of pathologic staging, is that earlier involvement of posterior cortical regions and the dorsal and ventral visual pathways (with or without visual hallucinations) are reliable markers for cognitive progression. To date, there have been few longitudinal and MRI studies focused on biomarker identification signaling cognitive progression in PD. Neuroimaging techniques offer promise in detecting neuronal changes before performance decrements and identifying biomarkers of accelerated cognitive progression.

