## Methods

### Overview

The primary objective is to investigate the prognostic value of PD-MCI subtypes and genetic variation in predicting the relative risk for progression to dementia utilizing a prospective longitudinal cohort followed for over 4 years. Tables 1 and 2 provide a detailed screening assessment and dependent study measures and timeline. The objectives will be addressed through the following methods: (1) neuropsychological evaluations and novel visuoperceptual tasks will be given annually for 4 years to nondemented PD patients (at baseline), and the predictive validity of visuoperceptual cognitive deficits relative to memory and executive deficits and ideal cutoffs (−1.5 vs −2 SD) for reliable prediction will be determined; (2) an exploratory genetic analysis of how variations in the *SNCA* (α-synuclein), *MAPT* (microtubule-associated tau), and *APOE* (apolipoprotein E) genes influence cognitive progression will be conducted; (3) the utility of task-activated functional magnetic resonance imaging (fMRI) as a probe for the risk for cognitive progression will examine altered posterior cortical networks before clinical manifestation; and (4) the anatomical and regional brain activation patterns predictive of cognitive progression will be determined.

Screening and recruitment will be conducted as outlined with year of testing denoted by 1-4. If we have attrition related to completing the MRI protocol or patients do not return for years 2-4, we will recruit additional patients in year 3 to ensure adequate numbers of patients and converters. The fifth year will be utilized for completion of data collection to account for attrition, image processing, and data analysis.

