### Statistical Analysis and Power

A sample of 120 PD patients is planned for this study. On the basis of the experience of longitudinal studies in PD, the attrition (mortality and loss to follow-up) is anticipated at 16% for 4 years. Thus, initial recruitment of 120 patients will yield about 100 subjects after 4 years. On the basis of published data, we estimate 70% PD-NC and 30% PD-MCI patients in our sample, and conversion rates of 60% from NC to MCI and 80% from MCI to PDD after 4 years. One of our primary goals is to evaluate progression patterns to determine time-specific differences between groups (NC vs MCI at baseline and PDD vs MCI, MCI vs NC, and PDD vs NC at year 4). Our study will have 80% power to detect medium-to-large average differences across time between the different groups under various within-subject correlations. In terms of predictive models for 4-year outcomes, our study will have 90% power to detect at least 0.86 area under the receiver operating characteristics curve (AUROC) for PDD conversion and 95% power to detect at least 0.74 AUROC for MCI at year 4.

To study differential cognitive progression patterns, generalized estimating equations will be used for describing the longitudinal trajectories of neuropsychological and visuoperceptual performances between PD-NC and MCI groups comparing baseline performance with different time points. The model will provide estimates of PD-MCI versus PD-NC differences at specific time points and longitudinally. Covariates such as age, UPDRS, and visual illusions or hallucinations will be added to the model to enable determination of adjusted differences.

We will investigate the prognostic value of baseline cognition in predicting relative risk for progression to PDD through a multiple logistic regression model. The best combination of baseline measures and covariates included in the prediction model will be selected by the elastic net procedure. Summary statistics of the AUROC will be used to evaluate the predictive power. Sensitivity, specificity, positive predictive value, and negative predictive value will be calculated from the optimal threshold determined by the Youden index. The prediction models will be cross-validated by training and testing methodology.

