## Discussion

### Overview

Cardinal features of idiopathic PD include motor symptoms attributed to dopaminergic depletion of the dorsal striatum. Nonmotor features of the disease such as cognitive impairment are common early in the disease process and can dominate in advanced stages, creating significant disability and poor quality of life. Follow-up studies reveal that MCI is present in one-third of the patients and can progress at variable rates to PDD. After 15 to 20 years, more than 80% of patients with MCI are diagnosed with PDD [2]. However, the neural and pathophysiologic mechanisms underlying variable cognitive deficits and their progression in PD remain poorly understood. Cognitive profiles in nondemented early-stage PD can be widespread, extending beyond expected frontostriatal circuitry. Furthermore, DRT can have a paradoxical effect on attention and memory, with evidence for overdosing of nondepleted ventral striatal circuits early in the disease process, suggesting that these deficits may be unreliable predictors of cognitive progression [9,10]. PD-MCI is heterogeneous in clinical presentation (executive, memory, and visuospatial), reflecting the presence of extranigral pathology in addition to dopamine. The co-occurrence of LB inclusions (α-synuclein) and Alzheimer pathology (amyloid-β and tau) is essential for the development of PDD, but the neurobiological basis of PD-MCI is unknown. Density of amyloid-β is predictive of neocortical atrophy, but how the predominate pathology in PDD (α-synuclein) influences clinical features or signals conversion to dementia is unclear.

Our central hypothesis, based on models of pathologic staging, is that earlier involvement of posterior cortical regions and the dorsal and ventral visual pathways (with or without the presence of visual hallucinations) are reliable markers for future cognitive progression. Our strategy toward this overarching goal is to characterize cognitive, genetic, and neural network progression in PD over a 4-year period. This allows evaluation of variable timing of onset and accelerated rates of cognitive progression, reflecting a deviation from expected stages of progression. Prospective longitudinal studies are essential to identify the initial cognitive symptoms and temporal pattern of atrophy and neural progression predictive of outcomes. These studies have been lacking, with overreliance on cross-sectional motor and pathological dementia studies in PD [7,20].

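### The study seeks markers of faster conversion to dementia, but its conversion model uses only 4-year status and ignores the year in which dementia appears

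*Protocol article*

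**What the plan says.** The Objectives section of the protocol article names, as a long-term aim, "identification of genetic and magnetic resonance imaging (MRI) markers signaling more rapid conversion to dementia". The Discussion (Overview) says of the design: "This allows evaluation of variable timing of onset and accelerated rates of cognitive progression". The Abstract (Objective) and the Discussion section on cognitive progression also speak of accelerated or rapid progression.

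The primary objective in Methods (Overview) has no element of speed. It is to "investigate the prognostic value of PD-MCI subtypes and genetic variation in predicting the relative risk for progression to dementia".

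Statistical Analysis and Power fixes the conversion model: "We will investigate the prognostic value of baseline cognition in predicting relative risk for progression to PDD through a multiple logistic regression model". Predictors are chosen by elastic net, and performance is summarised by AUROC, a Youden threshold, sensitivity, specificity and predictive values. The power statement for these models refers to 4-year outcomes. The planning rates are "conversion rates of 60% from NC to MCI and 80% from MCI to PDD after 4 years".

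The Timeline section and Table 2 schedule neuropsychological assessment in each of years 1 to 4. No analysis of time to PDD is described. The generalized estimating equations compare test-score trajectories between the baseline NC and MCI groups.

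**The concern.** A marker of rapid conversion separates patients who become demented early from those who become demented late or not at all. A yes/no outcome at 4 years keeps only the contrast between converting and not converting. Annual visits make the year of conversion observable, but the model does not use it.

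The loss is greatest where most patients convert, because the few non-converters then carry all the information. On the plan's rates that is the baseline-MCI group, in which the subtypes named in the primary objective are defined. The longitudinal model does not fill the gap: it describes scores by baseline group and neither models the onset of PDD nor predicts it from baseline markers.

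**Working it through.** **Inputs from Statistical Analysis and Power.** 120 recruited, 16% attrition over 4 years, 30% MCI and 70% NC at baseline, 80% of MCI converting to PDD and 60% of NC to MCI, 90% power at AUROC 0.86 for PDD, 95% power at AUROC 0.74 for MCI.

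**1. Counts.** 120 × 0.84 = 100.8, about 100 completers. Baseline MCI: 100 × 0.30 = 30. Converters: 30 × 0.80 = 24. Non-converters: 6. PDD among all completers: 24/100 = 24%.

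**2. The plan's own power figure.** Hanley-McNeil variance, null AUROC 0.5, two-sided 0.05 (assumed; the article states no alpha). With a = A/(2 − A) and b = 2A²/(1 + A),

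Var = [A(1 − A) + (n₁ − 1)(a − A²) + (n₀ − 1)(b − A²)]/(n₁n₀).

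- 24 v 6, A = 0.86: (0.1204 + 23 × 0.0148 + 5 × 0.0557)/144 = 0.00513, SE 0.0716; null SE 0.1339. z = (0.36 − 1.96 × 0.1339)/0.0716 = 1.36, power 91.3% (stated 90%).
- 24 v 76, A = 0.86: SE 0.0504, null SE 0.0679, z = 4.50, power about 100%. This does not match.
- Companion figure, 42 v 28 within baseline NC, A = 0.74: power 95.8% (stated 95%).

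The stated PDD power is therefore consistent with a model within baseline MCI that has six non-cases.

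**3. What the yes/no outcome merges.** With a constant hazard giving 80% at 4 years, the annual probability is 1 − 0.2^(1/4) = 33.1%. The 30 MCI patients convert as about 9.9, 6.6, 4.4 and 3.0 in years 1 to 4. By year 2, 1 − 0.669² = 55% of the group has converted. The logistic model codes all 24 alike.

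**4. Illustrative power.** Assumed, not in the document: a subtype of 10 against 20 others, hazard ratio 3, exponential times read at four annual visits, no dropout, two-sided 0.05. The baseline hazard is solved to give the overall conversion shown. Repeat runs differ by one to two points.

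| Overall conversion | Year-4 rates, subtype v rest | Year-4 status, chi-square | Year-4 status, likelihood ratio | Time to conversion, log-rank |
|---|---|---|---|---|
| 80% | 98% v 71% | 28% | 58–60% | 72–73% |
| 60% | 85% v 47% | 54% | 60% | 65% |
| 40% | 63% v 28% | 46% | 46–48% | 49–51% |

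Type I error at 80% conversion is about 4% for chi-square, 7% for likelihood ratio and 5.5% for log-rank. The likelihood-ratio test is the one that belongs to logistic regression; it is slightly liberal here.

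**5. Would a whole-cohort model avoid the problem?** If no NC patient reaches PDD, as the planning rates imply, all 24 cases and 6 of the 76 non-cases have MCI at baseline. The baseline MCI flag alone then gives AUROC (1 + 70/76)/2 = 0.96, above the 0.86 target, and timing is still unused.

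**The case against.** The strongest reply is that the primary objective is worded as relative risk, which a 4-year status model addresses, and that rapid conversion is a long-term objective. Against the course over 15 to 20 years cited in the Background, PDD within 4 years is itself a usable definition of rapid. This stands: the mismatch is with the rapid-conversion aim, not with the primary objective as worded.

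It is also fair that the plan judges prediction by AUROC and cross-validation and proposes no test of one subtype against the rest. The power comparison only illustrates how much information is lost.

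Three stronger readings are tempting and are not supported.

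- A reader might infer that a minority subtype's prognosis could never be shown. Under Fisher's exact test, 10/10 v 14/20 gives p = 0.074 and 12/12 v 12/18 gives 0.057. The plan specifies logistic regression, whose likelihood-ratio test gives 0.018 and 0.008. Only a subtype of 6 (6/6 v 18/24) stays above 0.05, at 0.082.
- A reader might infer that a marker of earlier dementia leaves almost no trace in year-4 status. The illustration itself shows 98% v 71%.
- A reader might set Fisher's 16% power against the log-rank figure. Most of that contrast comes from Fisher's conservatism (type I error about 2%), not from ignoring timing.

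Nor does near-saturation hold for the whole cohort, where PDD is about 24%.

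**Conclusion.** The point holds as a worthwhile, inexpensive improvement; it does not show that the planned model is invalid. The aim concerns speed, the outcome is status at one time, and the year of conversion is collected but not used in the conversion model.

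Within baseline MCI at the plan's 80% conversion, using the year would raise illustrative power from between 28% and 60%, depending on the test, to about 72%. At 40 to 60% conversion the gain is about 3 to 11 points.

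The size depends on the assumed subtype split, hazard ratio, constant hazards and four annual intervals, and above all on the 80% rate. The article elsewhere cites conversion above 80% only after 15 to 20 years. Taking exactly 80% at a constant hazard, that would mean 1 − 0.2^(4/20) = 28% to 1 − 0.2^(4/15) = 35% at 4 years. The efficiency gain would then be small, although the model would still not address speed.

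**What to change.** Record at each annual visit, from the battery already given, whether PDD is diagnosed, and define the outcome for the rapid-conversion aim as the visit of first diagnosis. Fit a discrete-time (complementary log-log) hazard model with the same elastic-net selection, and report hazard ratios and time-dependent AUROC by year. Keep the year-4 logistic model and its AUROC for the relative-risk objective in Methods (Overview).

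The cost is analysis wording and an annual diagnosis, with no new patients, visits or tests. The hazard model also uses the follow-up of patients lost before year 4, about 20 of 120 on the plan's attrition. The downside is a proportional-hazards assumption to check, and censoring at loss or death has to be justified.

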### Exclusion Criteria

(1) Other neurologic disorder or stroke; (2) dementia (MoCA <21 at baseline) or functional decline on instrumental ADLs related to cognitive deficits [27]; (3) major psychiatric disorder, including alcohol or substance abuse; (4) concurrent, unstable or serious medical condition; (5) major head trauma; (6) chronic use of psychoactive medications; (7) significant dyskinesia on neurological examination; (8) tremor greater than 2 for upper extremities and head tremor greater than 1 based on the MDS-UPDRS on neurological examination; and (9) claustrophobia, pacemaker, neurostimulator, or other implants or other factors that interfere with the ability to lay still in the MRI scanner for 1 hour.

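### The year-4 prediction models are judged by AUROC with no baseline-level comparator, so a high value would not by itself identify a marker of faster cognitive progression

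*Protocol article*

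**What the plan says.** The main prediction analysis is in Statistical Analysis and Power: "We will investigate the prognostic value of baseline cognition in predicting relative risk for progression to PDD through a multiple logistic regression model". Baseline measures and covariates are chosen by elastic net, AUROC summarises predictive power, and the models are cross-validated. The power statement covers two year-4 outcomes: AUROC 0.86 for PDD conversion (90% power) and 0.74 for MCI (95% power). The planning figures are "initial recruitment of 120 patients will yield about 100 subjects after 4 years", a baseline mix of 70% NC to 30% MCI, and "conversion rates of 60% from NC to MCI and 80% from MCI to PDD after 4 years".

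The Methods Overview gives the primary objective as predicting the relative risk of progression to dementia. The abstract's Objective, the Objectives section and the Discussion Overview go further and ask for markers of more rapid or accelerated progression. The Discussion says of the strategy: "This allows evaluation of variable timing of onset and accelerated rates of cognitive progression".

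Neuropsychological and visuoperceptual testing is repeated annually. The separate GEE analysis compares trajectories between the baseline NC and MCI groups.

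Two sets of cognitive cutoffs appear. The Methods Overview says "ideal cutoffs (−1.5 vs −2 SD) for reliable prediction will be determined", and the Exclusion Criteria list "dementia (MoCA <21 at baseline) or functional decline on instrumental ADLs related to cognitive deficits". Neither is given as the rule for assigning the year-4 category.

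**The concern.** Risk of being in a worse category at year 4 and speed of decline are different quantities. A patient who starts lower is more likely to be classed as MCI or PDD four years later even if everyone declines at the same average rate. A baseline measure that tracks current cognitive level will therefore predict the year-4 category without carrying any information about rate.

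The plan describes no model that holds baseline level fixed and no AUROC gain over it. The GEE analysis does not fill the gap, because it contrasts baseline groups and does not relate any marker to a patient's own decline.

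At stake is the interpretation of the headline result. A visuoperceptual, imaging or genetic measure with a good AUROC could be reported as signalling accelerated progression when it only reflects who was already impaired.

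**Working it through.** **Inputs from Statistical Analysis and Power.** Attrition is 16%, so 120 × 0.84 = 100.8, or about 100 completers. The 70/30 split gives 70 baseline NC and 30 baseline MCI. Conversion gives 0.60 × 70 = 42 NC to MCI and 0.80 × 30 = 24 MCI to PDD. No NC-to-PDD rate is stated.

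**Assumptions.** The power statement gives no alpha or null value; I take two-sided 0.05 against AUROC 0.5. The baseline-to-year-4 score correlation r is not given; I show a range.

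**Step 1: reproduce the stated power.** The null variance is (n1 + n0 + 1)/(12·n1·n0). The variance under the alternative A is Hanley-McNeil: [A(1−A) + (n1−1)(Q1−A²) + (n0−1)(Q2−A²)]/(n1·n0), where Q1 = A/(2−A) and Q2 = 2A²/(1+A). Power is Φ[(A − 0.5 − 1.96·SE0)/SE_A].

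- PDD, 24 v 6 within baseline MCI, A = 0.86: SE0 = √(31/1728) = 0.134 and SE_A = 0.0716. Power = Φ[(0.36 − 0.2625)/0.0716] = 0.913 (stated 0.90).
- MCI, 42 v 28 within baseline NC, A = 0.74: SE0 = √(71/14112) = 0.0709 and SE_A = 0.0585. Power = Φ[(0.24 − 0.139)/0.0585] = 0.958 (stated 0.95).
- Whole-cohort sets do not match: 24 v 76 gives power 1.00 and 42 v 58 gives 0.99.

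The power figures therefore fit analyses within baseline strata. The text on the logistic model does not state that restriction.

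**Step 2: PDD in the whole cohort, baseline MCI/NC label as the only predictor.** For a binary predictor, AUROC = (sensitivity + specificity)/2. If a proportion p of the 70 NC patients reach PDD, sensitivity = 24/(24 + 70p) and specificity = (70 − 70p)/(76 − 70p).

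| p | Sensitivity | Specificity | AUROC |
|---|---|---|---|
| 0 | 24/24 = 1.000 | 70/76 = 0.921 | 0.961 |
| 5% | 24/27.5 = 0.873 | 66.5/72.5 = 0.917 | 0.895 |
| 8% | 24/29.6 = 0.811 | 64.4/70.4 = 0.915 | 0.863 |
| 10% | 24/31 = 0.774 | 63/69 = 0.913 | 0.844 |

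This step needs no assumption about how PDD is scored.

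**Step 3: within each stratum, baseline score as the only predictor.** Baseline and year-4 scores are simulated as bivariate normal with correlation r. The mean decline is common to all, and individual slopes do not depend on baseline true level. Baseline MCI is the lowest 30%, and the year-4 cut is set to give the plan's conversion rate in each stratum. Scoring year 4 by a cut on the repeated score is an assumption of this step.

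| r | MCI within baseline NC (60% convert) | PDD within baseline MCI (80% convert) |
|---|---|---|
| 0.50 | 0.67 | 0.62 |
| 0.65 | 0.74 | 0.67 |
| 0.70 | 0.77 | 0.69 |
| 0.80 | 0.83 | 0.74 |
| 0.90 | 0.91 | 0.80 |
| 0.95 | 0.95 | 0.86 |

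Nothing in this simulation uses a marker of faster decline. For comparison, the smallest AUROC significantly above 0.5 is 0.5 + 1.96 × 0.0709 = 0.64 for 42 v 28, and 0.5 + 1.96 × 0.134 = 0.76 for 24 v 6.

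**The case against.** **The primary objective is risk prediction.** For that purpose baseline cognition is a legitimate predictor and a high AUROC is a proper result. This stands, and is why the risk model should be kept. It does not cover the claims about more rapid or accelerated progression.

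**The year-4 scoring rule is not stated.** A reader might infer that conversion means crossing a fixed cutoff on the same battery. The documents do not support that. The SD cutoffs concern baseline deficits used for prediction. The MoCA rule is a baseline exclusion with a functional-decline limb, and instrumental activities are reassessed annually. A condensed article may leave the year-4 definition to the full protocol. Step 2 does not depend on it; step 3 does.

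**The values 0.86 and 0.74 are not pass marks.** They are AUROCs detectable at the stated power. To say the study could pass its target with no marker misreads them.

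**The effect is smaller where the PDD power calculation sits.** In the 24 v 6 set, baseline nearness reaches 0.86 only at r near 0.95. This stands and limits the point for PDD within baseline MCI.

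**The visuoperceptual hypothesis is not favoured by construction.** That stronger reading also fails. Visuoperceptual deficits are judged relative to memory and executive deficits, elastic net selects jointly, and any near-threshold advantage is shared across the battery. Genetic and MRI predictors are not battery scores, though they may still correlate with baseline level.

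**Replacing the outcome with change from baseline is not a clean cure.** Raw change shares measurement error with the baseline score, and regression to the mean then biases against the same tests.

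**Conclusion.** The point holds in a limited form. AUROC for the year-4 category, with no baseline-level comparator, cannot support a claim that a marker signals faster progression.

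The size depends on the analysis set. In the whole cohort, the baseline label alone gives 0.96 for PDD with no direct NC-to-PDD conversion, and stays at or above 0.86 until about 8% of NC patients reach PDD. Within baseline NC, the baseline score alone gives 0.67 to 0.83 for MCI at correlations of 0.50 to 0.80. Within baseline MCI, it gives 0.62 to 0.74 for PDD over the same range. The correlation and the NC-to-PDD rate are assumptions, and the within-stratum figures also assume a cut on the repeated score.

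This is a worthwhile, inexpensive improvement. It does not show that the risk model is wrong or that the stated power is in error.

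**What to change.** Keep the logistic and elastic-net risk model, and make two additions.

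1. Fit a reference model containing baseline cognitive level: baseline NC/MCI status plus MoCA or a battery composite. Report the cross-validated AUROC gain of the visuoperceptual, imaging and genetic markers over it. Describe a measure as a marker of accelerated progression only if it adds to that model. State the analysis set for each outcome; where it is a single baseline stratum, the status term drops out and the continuous score carries the adjustment.
2. As a supporting analysis, relate each marker to individual cognitive slope in a longitudinal model of the annual scores, through a marker-by-time interaction. This avoids regressing raw change on a baseline score that shares its error.

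The cost is analysis wording and programming only, since the annual data are already planned. The gains will be smaller and less precise than the raw AUROCs, especially for PDD with 30 baseline MCI patients and about 6 non-converters, so intervals should accompany them.
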